#### Step three: virtual reality training and evaluation.

Following informed consent, the 40 healthcare professionals not involved in the scenario co-design focus group will participate in a single-arm, pre-post study evaluating the effectiveness of a VR-based communication training program.

Each participant will attend one individual single-session lasting approximately 2 hours, scheduled within a 10-day period. Two sessions will be held each day (9:30–11:30 am and 2:00–4:00 pm), ensuring participant availability across day and night shifts.

At the start of the session, participants will complete the “Verbal and Nonverbal Communication Training Needs Questionnaire” (see S3 Text) to assess their self-perceived communication challenges related to the management of patients with behavioral and psychological symptoms of dementia (BPSD).

They will then proceed to view the first immersive VR scenario using a 3D headset, based on content co-developed during the scenario co-design phase. Immediately afterward, they will complete a multiple-choice quiz evaluating their understanding of verbal and nonverbal communication strategies illustrated in the scenario.

A debriefing session with psychologist investigators will follow, to discuss the participant’s quiz responses and provide tailored feedback.

Participants will then access a reinforcement module on Moodle, designed to consolidate the key theoretical concepts presented in the first scenario.

This sequence (VR viewing → quiz → debriefing → Moodle training) will be repeated for a second VR scenario, followed again by a debriefing and Moodle reinforcement.

At the end of the training session, participants will complete the post-training assessments, including:

satisfaction with the training experience,perceived competence in managing BPSD,and perceived pedagogical effectiveness of the VR scenarios.

The full process is presented in Fig 3.

**Fig 3 pone.0325910.g003:**
[figure not shown]
Workflow chart of the study protocol design. Overview of the sequence of procedures, including baseline questionnaires, VR scenarios, debriefings, Moodle-based reinforcement, and post-training assessments.

#### Step four: assessments.

After each VR scenario, participants will complete a multiple-choice quiz to assess their knowledge of appropriate verbal and nonverbal communication strategies with patients suffering from BPSD. The quiz scores, based on the percentage of correct responses, will be calculated separately for Scenario 1 and Scenario 2. These scores will be returned to participants to help track their progress and knowledge acquisition.

The primary outcome of the study, the pedagogical effectiveness of the training, will be measured by the improvement in participants’ knowledge scores between Scenario 1 and Scenario 2 (see calculation method in the *Data collection and assessment tools* section).

Participants will also complete questionnaires evaluating:

their overall satisfaction with the training method (VR scenario movies and Moodle reinforcement),their self-perceived level of competence.

In addition, they will complete two supplementary questionnaires:

one assessing satisfaction with the VR scenarios, andanother evaluating the usability of the 3D VR training method (see details in *Data collection and assessment tools*).

The total time required to complete all assessments will not exceed 1 hour.

### Training tools

#### VR-based training program and Moodle reinforcement.

The training program combines immersive 3D virtual reality (VR) scenarios with structured Moodle-based theoretical reinforcement. The aim is to enhance participants’ ability to communicate effectively with patients displaying disruptive behavioral and psychological symptoms of dementia (BPSD), such as agitation, aggressiveness, or care refusal.

The two VR scenarios, co-designed with healthcare professionals, depict realistic care situations where verbal and nonverbal communication is challenged. After viewing each scenario, participants complete a quiz to assess their understanding of appropriate and inappropriate caregiver behaviors.

To consolidate the learning, each VR scenario is followed by a Moodle-based module. These modules provide structured theoretical content that helps participants:

analyze the clinical situations observed in the VR scenes,interpret patient-caregiver interactions in light of BPSD-related challenges,and identify appropriate verbal and nonverbal communication strategies.

Topics covered include:

the use of simple language, open-ended questions, and validation therapy,how to respond to patients with language or cognitive impairments,and how to manage communication during episodes of aggression or care refusal using active listening, reassurance, and de-escalation techniques.

The Moodle platform also offers guidance on behaviors to avoid, such as ambiguous gestures or rushed interactions, which can exacerbate patients’ distress. Overall, this combined approach aims to equip healthcare professionals with the knowledge, strategies, and reflective tools needed to improve their interactions with patients experiencing disruptive BPSD.

### Data collection and assessment tools

#### Evaluation of healthcare professionals’ training needs in verbal and nonverbal communication (V/NV).

At baseline, all participants will complete a self-administered training needs questionnaire specifically designed for this study (see S3 Text). The purpose of this tool is to assess the participants’ initial knowledge, training background, and expectations regarding communication with patients presenting behavioral and psychological symptoms of dementia (BPSD).

The results of this baseline assessment will help contextualize the learning process and, if necessary, fine-tune the Moodle content used to reinforce the VR scenarios.

The questionnaire includes items that evaluate the participants’ general understanding of communication challenges specific to patients with BPSD, the types of training previously completed in the field of relational care and behavioral disorders, and prior experience with digital learning technologies, including virtual reality simulation, in accordance with the recommendations of the French Haute Autorité de Santé (December 2019) [46].

Demographic information will also be collected, including age, professional role, and years of experience. This data will provide insight into the training needs across different staff profiles and contribute to the interpretation of post-training outcomes.

#### The satisfaction of participants with the training methods.

Participants’ satisfaction with the training program will be assessed at the end of the training session, following the completion of the VR scenarios, quizzes, debriefings, and Moodle modules. They will be asked to rate their overall satisfaction with the training they received using a 5-point Likert scale, where 1 indicates “very unsatisfied” and 5 indicates “very satisfied.”

This evaluation will provide insight into the perceived relevance, clarity, and usefulness of the immersive VR experience combined with theoretical reinforcement through the Moodle platform.

#### The evaluation of the participant’s satisfaction of the two VR scenarios.

All participants will be asked to complete a scenario-specific satisfaction questionnaire, developed by the research team (see S4 Text), to assess their experience with each of the two immersive VR scenarios.

This questionnaire will gather feedback on elements such as:

the realism and relevance of the scenarios,the emotional engagement generated by the immersive content,and the perceived usefulness of the scenarios in improving real-life communication with patients with BPSD.

**To assess the usability of the VR 3D training method**, the System Usability Scale (SUS) will be employed [47]. The SUS provides a subjective viewpoint of the user on the system and its ease of use on a 5-point Likert-type scale ranging from 1 to 5. The total is calculated using the SUS questionnaire and ranges from 0 to 100, with a higher score indicating greater usability satisfaction [47].

**The learners’ self-perceived level of competence** will be quantitatively analyzed using a questionnaire created by the researchers (see S5 Text) which is based on the “perceived competence” section of the “Intrinsic Motivation Inventory” [48]. This subsection evaluates motivation and competence in a multidimensional way. The results will be reported on a 5-point Likert-type scale, ranging from 1 to 5. A higher total score indicates a greater sense of acquired competence.

**The evaluation of the pedagogical effectiveness of the training will be based on** the participants’ The pedagogical effectiveness of the training will be assessed by measuring participants’ knowledge progression between Scenario 1 and Scenario 2 of the immersive VR training. After viewing each scenario, participants will complete a multiple-choice quiz, and the learning platform will automatically calculate their scores:

Score 1 after Scenario 1,Score 2 after Scenario 2.

The difference between Score 2 and Score 1 will be used as an indicator of knowledge acquisition:

If Score 2 ≤ Score 1, no learning progress is observed,If Score 2 > Score 1, the participant is considered to have improved in knowledge and understanding of appropriate communication strategies.

This within-subject comparison provides a direct measure of the training tool’s educational value and its effectiveness in reinforcing verbal and nonverbal communication skills relevant to the management of patients with disruptive BPSD.

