**Methods:**

The training scenarios were co-designed with ten healthcare professionals and implemented using an immersive 3D VR platform. Forty geriatric healthcare professionals will participate in a 2-hour training session using VR movies and a Moodle-based theoretical reinforcement. Before and after the training, participants will complete self-assessment questionnaires and knowledge-based quizzes designed to evaluate their perceived competence and understanding of appropriate communication strategies with patients displaying BPSD. The primary outcome will be the change in quiz scores between the pre- and post-training evaluations. Secondary outcomes include training satisfaction, perceived competence, and system usability.

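### The primary outcome is labelled a before-to-after training change but is computed as Score 2 minus Score 1, which spans only part of the programme and mixes in any difference between the two quizzes

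*Protocol article*

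**What the plan says.** The abstract (Methods) states: "Before and after the training, participants will complete self-assessment questionnaires and knowledge-based quizzes". It continues: "The primary outcome will be the change in quiz scores between the pre- and post-training evaluations". The title and the section Design and setting also describe a pre-post comparison that includes knowledge.

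The workflow under Step three is different. The session opens with a training-needs questionnaire, followed by the first VR film. Then: "Immediately afterward, they will complete a multiple-choice quiz evaluating their understanding of verbal and nonverbal communication strategies illustrated in the scenario". A debriefing on the quiz answers and a Moodle module follow. "This sequence (VR viewing → quiz → debriefing → Moodle training) will be repeated for a second VR scenario". The session closes with forms on satisfaction, perceived competence and perceived pedagogical effectiveness.

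Step four measures the primary outcome as the improvement in "knowledge scores between Scenario 1 and Scenario 2". The paragraph on pedagogical effectiveness, in Data collection and assessment tools, repeats this: "After viewing each scenario, participants will complete a multiple-choice quiz, and the learning platform will automatically calculate their scores". It takes Score 2 minus Score 1, counts a participant as showing no progress when Score 2 does not exceed Score 1, and describes the comparison as directly measuring the tool's educational value. Primary analysis applies a paired t-test to the same two scores.

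**The concern.** Two definitions of the primary outcome stand side by side, and the one that will be computed does not match the stated objective. A before-to-after comparison needs a score taken before any training and one taken after all of it. Neither Score 1 nor Score 2 is such a score.

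Three consequences follow:

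- A null result could hide a real gain already made from film 1.
- A positive result could reflect an easier second quiz or practice with the quiz format.
- Even a genuine gain could not be credited to VR, because a debriefing and a Moodle module lie between the scores.

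A baseline that is not collected cannot be recovered at analysis, so the matter has to be settled before the first session.

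**Working it through.** **Step 1. Order of events (Step three).**

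| Order | Event | Between Score 1 and Score 2? |
|---|---|---|
| 1 | Training-needs questionnaire | no |
| 2 | VR film 1 | no (before Score 1) |
| 3 | Quiz 1 = Score 1 | – |
| 4 | Debriefing 1 on quiz answers | yes |
| 5 | Moodle 1 | yes |
| 6 | VR film 2 | yes |
| 7 | Quiz 2 = Score 2 | – |
| 8 | Debriefing 2 | no (after Score 2) |
| 9 | Moodle 2 | no (after Score 2) |
| 10 | End-of-session forms | no |

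**Step 2. What the contrast contains.** Let K be knowledge on arrival, and let F1, D1, M1, F2, D2, M2 be the gains from each film, debriefing and module. Let q1 and q2 be quiz-specific shifts (content, difficulty, practice with the format). If the gains accumulate:

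- Score 1 = K + F1 + q1
- Score 2 = K + F1 + D1 + M1 + F2 + q2
- Score 2 − Score 1 = D1 + M1 + F2 + (q2 − q1)
- Whole programme effect = F1 + D1 + M1 + F2 + D2 + M2

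The contrast omits F1, D2 and M2 and adds q2 − q1. The quizzes are scored separately by scenario, are taken in one fixed order, and are not stated to be equivalent, so nothing sets q2 − q1 to zero.

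**Step 3. The no-progress rule.** Score 2 ≤ Score 1 whenever D1 + M1 + F2 + (q2 − q1) ≤ 0, whatever the size of F1. A participant who learned a great deal from film 1 and then scored equally high twice is classed as having made no progress.

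**Step 4. The plan's own sample size.** Inputs from Sample size justification: dz = 0.5, two-sided 5%, 80% power, paired t-test. Power is the probability that a noncentral t with n − 1 degrees of freedom and noncentrality dz × √n falls beyond the two-sided critical value.

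- n = 34: noncentrality 0.5 × √34 = 2.92, power 80.8%. The stated minimum of 34 reproduces.
- n = 40: noncentrality 0.5 × √40 = 3.16, power 86.9%.

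The arithmetic is sound. The question is which contrast the 0.5 applies to.

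**Step 5. Sensitivity to the share captured (assumed; not in the protocol).** Suppose the whole before-to-after effect is dz = 0.5, the SD of the differences is unchanged, and the contrast captures only a share of the effect. At n = 40:

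| Share captured | dz | Power |
|---|---|---|
| 100% | 0.5 | 86.9% |
| 75% | 0.375 | 63.8% |
| 50% | 0.25 | 33.8% |
| 25% | 0.125 | 12.0% |

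**Step 6. Sensitivity to unequal quizzes (also assumed).** Suppose nobody learns anything and quiz 2 is easier than quiz 1 by the stated multiple of the SD of differences. At n = 40 the test is then significant this often, against a nominal 5%:

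| Quiz 2 easier by | Significant |
|---|---|
| 0.1 SD | 9.5% |
| 0.2 SD | 23.5% |
| 0.3 SD | 45.7% |
| 0.5 SD | 86.9% |

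Conversely, if the contrast contains real learning of dz = 0.5 but quiz 2 is harder by 0.2 SD, the net dz is 0.3 and power is 45.7%.

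**The case against.** *The contrast is not empty.* Training tools defines the programme as films combined with Moodle, and debriefing belongs to the session. Score 2 minus Score 1 therefore spans real programme components. This stands. A reader might infer that the training effect is not measured at all, but the protocol supports only the narrower statement: part of the programme effect is measured, and neither the whole nor VR's share is.

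*Some quiz items need the film.* Step one includes items on recognising good and bad behaviour by the fictional caregiver, which cannot be answered before viewing. Score 1 can then be read as preceding any feedback, debriefing or Moodle. That is fair, but it still does not precede VR or training.

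*Other quizzes may exist.* The closing list is open-ended: "At the end of the training session, participants will complete the post-training assessments, including". Handling missing data names knowledge quizzes as an example of post-training assessments. Secondary analyses uses a before-training competence measure that Step three does not list, so the Step three lists are incomplete. The needs questionnaire is said to cover initial knowledge, and some figures and supplements are not shown. The absence of a quiz should therefore be stated as none described in the text shown. None of this alters the primary formula, which Step four, the pedagogical-effectiveness paragraph and Primary analysis all build from the two post-film scores.

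*The study is exploratory and admits having no control group.* Lack of a control group is a different limitation from lack of a pre-training score. The Discussion presents the pre-post design as a strength.

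Two further strong readings also go too far. One is that the VR effect cancels completely. That would require film gains that do not carry over, equal gains from both films, and equally difficult quizzes. The other is that power is 34%. That figure rests on an assumed 50% share, and the protocol offers dz = 0.5 only as a moderate effect for a paired design.

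**Conclusion.** The point holds. The abstract's before-to-after definition and the operational Score 2 minus Score 1 are different quantities, and the second has neither a pre-training nor a post-training score. It captures feedback and debriefing 1, Moodle 1 and film 2, confounded with differences between the two quizzes. It cannot support the description of the comparison as a direct measure of educational value, and the no-progress rule can misclassify participants who learned from film 1.

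The contradiction itself rests on the text alone. The size of the damage does not: about 64%, 34% or 12% power instead of 87% requires an assumed share of 75%, 50% or 25% and an unchanged SD of differences. The inflated rejection rates require an assumed difficulty gap. The sample-size calculation itself is correct.

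**What to change.** **Preferred.** Give one knowledge quiz that can be answered without having seen the films, before film 1 and again, in the same or an equated form, after Moodle module 2. Make post minus pre the primary outcome with the same paired t-test. For the same dz the minimum stays 34 and the planned number stays 40. Keep Scores 1 and 2 as secondary outcomes. Do not claim that comparing the pre-quiz with Score 1 isolates the VR effect: one quiz would be independent of the films and the other specific to a scenario, so the comparison would be between two instruments.

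**Cost.** Items must be written. The focus group that proposes quiz questions has not yet met, and the platform already scores quizzes. The few extra minutes must fit within the 120-minute cap on participation and the 1-hour cap on assessments. Some retest familiarity is unavoidable. The amendment needs IRB approval. According to Status and timeline, recruitment had not started and data collection was planned for September to December 2025.

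**If no pre-quiz is added.** Rename the primary outcome *between-scenario change*. Correct the abstract, Design and setting, and the pedagogical-effectiveness paragraph to match. Drop the pre/post knowledge and VR-effect claims. Beyond the IRB-approved amendment, this costs only text.

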### Protocol workflow

#### Step one: scenario design phase.

In this phase, 10 healthcare professionals (out of 50 participants) who have given written consent to participate in the study, will be invited to a focus group. The researchers (a couple of 2 psychologists and 2 geriatricians) will provide them two scenarios, each describing a clinical context involving a patient with disruptive BPSD (aggression, opposition, agitation, and/or anxiety) and a professional caregiver (example of a scenario in S2 Text). The scenarios will be written in a precise but concise manner, outlining situations where conflicts are likely to arise due to the patient’s non-cooperative behavior towards the caregiver (*e.g*., grooming with an unwilling patient or agitation during group activities).

Participants will be asked to provide feedback on the scenarios based on their own professional experience and knowledge, as well as to suggest modifications or additions to the dialogues and gestures of the fictional characters in order to either aggravate the conflict or soothe the patient, depending on the situation. To guarantee the pedagogical excellence of the scenarios, we will ensure that the experiences and knowledge of investigators, including doctors and psychologists, as well as healthcare personal involved in the focus group, are incorporated. Moreover, recommendations from health authorities and healthcare societies regarding the care of patients experiencing behavioral and psychological symptoms of dementia (BPSD) will also be taken into consideration. By doing so, the scenarios can be co-written with a well-rounded and comprehensive approach, taking into account various perspectives and expertise, thus ensuring their accuracy and effectiveness.

To evaluate later the pedagogical value of the scenarios, participants will be asked to propose multiple choice questions. These quizzes will be used to evaluate the subsequent participants for their ability to identify appropriate and inappropriate verbal and nonverbal communication by the fictional healthcare professional, as well as their knowledge about optimal ways to behave with demented patients with disruptive BPSD, as represented by the fictional patient in the scenarios.

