### Primary analysis

The main objective of the analysis is to evaluate the pedagogical effectiveness of the VR training program. This will be assessed through the comparison of knowledge quiz scores completed after each scenario (Score 1 and Score 2). The mean difference between these two scores will be calculated for each participant. A paired-sample t-test will be used to determine whether the change in knowledge is statistically significant, with a significance level set at *p* < 0.05.

This test is appropriate for the within-subjects design, where each participant serves as their own control.

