### Sample size justification

The sample size was determined based on an a priori power analysis for a paired-sample design. To detect a moderate effect size (Cohen’s dz = 0.5) with 80% power at a 5% significance level using a two-tailed paired t-test, a minimum of 34 participants was required. To allow for potential dropouts or incomplete data, we increased the sample size to 40 participants. The calculation was performed using G*Power (version 3.1). We plan to include 40 participants, allowing for possible attrition.

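### Calling every participant with Score 2 above Score 1 improved would label a large minority, about 34–45% under ordinary quiz assumptions, as having learned when nobody has

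*Protocol article*

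**What the plan says.** The Protocol article defines the pedagogical effectiveness of the training, its primary outcome, as the gain in knowledge between two quizzes. Each quiz is taken once, after a different VR scenario: "Score 1 after Scenario 1,Score 2 after Scenario 2". On the scale, Step four says: "The quiz scores, based on the percentage of correct responses, will be calculated separately for Scenario 1 and Scenario 2".

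Under Data collection and assessment tools, the difference between the scores is named as the indicator of knowledge acquisition. A rule for each participant follows. On one side, "If Score 2 ≤ Score 1, no learning progress is observed". On the other, "If Score 2 > Score 1, the participant is considered to have improved in knowledge and understanding of appropriate communication strategies". No minimum change is set, and ties fall on the no-progress side. The article then presents the comparison as a direct measure of the tool's educational value.

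The Primary analysis section works on the same difference but by another route: "A paired-sample t-test will be used to determine whether the change in knowledge is statistically significant", at the 5% level. The Sample size justification is built on that test with dz = 0.5 and 80% power: "a minimum of 34 participants was required", raised to 40. Neither the primary nor the secondary analyses include a test of the proportion labelled improved.

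The article does not state how many items a quiz has, what percent correct is expected, or whether the two quizzes are equally hard. The items are still to be written; in the scenario design phase, "participants will be asked to propose multiple choice questions".

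**The concern.** A single percent-correct score on a multiple-choice quiz carries error from guessing and from which items happen to be asked. The sign of the difference between two such scores is therefore partly noise. A person whose knowledge has not moved will score higher on the second quiz about as often as lower, and the rule reads each such rise as a gain in knowledge.

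The error also runs the other way. A participant who has learned may tie or score lower by chance and be recorded as showing no progress. Anyone with full marks on the first quiz, which is taken after the first film, cannot be recorded as improved.

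At stake is how the results are read. The study has no control group, as its own limitations section says, so a reader would have no chance rate to set beside a share of participants called improved. The article plans infographics and a report to hospital management, where such a share could easily be taken as evidence of benefit.

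**Working it through.** **1. The plan's own figure.** Inputs from the Sample size justification: dz = 0.5, two-sided 5% level, 80% power, paired t-test. Power at n is the probability that a noncentral t variable with n − 1 degrees of freedom and noncentrality 0.5·√n falls outside ± the 97.5% t quantile.
- n = 33: 79.5%
- n = 34: 80.8%
- n = 40: 86.9%

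The smallest n reaching 80% is 34, so the stated minimum reproduces. It rests on the mean difference alone; the improved label does not enter.

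**2. Chance rate of the label.** Suppose no learning, two quizzes of m items each, and the same probability p of a correct answer on both. The scores are then independent Binomial(m, p), and by symmetry

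P(Score 2 > Score 1) = (1 − P(tie)) / 2.

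Example: m = 5, p = 0.8 has P(tie) = 0.320, giving (1 − 0.320)/2 = 34.0%.

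Both m and p are assumptions, because the article gives neither. Share labelled improved with no learning (%):

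| Items per quiz | p = 0.5 | 0.7 | 0.8 | 0.9 | 0.95 |
|---|---|---|---|---|---|
| 3 | 34.4 | 32.6 | 29.1 | 20.4 | 12.3 |
| 5 | 37.7 | 36.4 | 34.0 | 26.9 | 18.0 |
| 10 | 41.2 | 40.3 | 38.8 | 34.4 | 26.8 |
| 20 | 43.7 | 43.1 | 42.1 | 39.3 | 34.5 |
| 30 | 44.9 | 44.4 | 43.6 | 41.3 | 37.7 |

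For 5–30 items and 50–80% correct the range is 34.0–44.9%. In 40 participants that is 40 × 0.340 = 13.6 to 40 × 0.449 = 18.0, or about 14 to 18 people. Over the whole table it is about 12–45%. With equal-length, equally hard quizzes the limit is 50%, reached as ties vanish.

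**3. Departures from those assumptions, still with no learning.**
- Participants differing in ability (beta-distributed p), 10 items: 38–40% at a mean of 0.7, and 24–31% at a mean of 0.9.
- Quizzes of unequal length, p = 0.7: 45.9% (10 then 9 items) and 48.3% (10 then 12), because ties almost disappear.
- Second quiz easier by 5–10 points, from p = 0.7, 5–20 items: 43–71%.
- Second quiz harder by 5–10 points, same settings: 20–32%.

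**4. The opposite error.** A true gain of 10 points from p = 0.7 on equally hard quizzes has the same arithmetic as a second quiz that is 10 points easier. With 10 items, 60.4% are labelled improved, so 100 − 60.4 = 39.6% are labelled as showing no progress although everyone gained.

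**5. Ceiling.** With 10 items the chance of full marks on the first quiz is p to the power 10: 0.6% at p = 0.6, 2.8% at 0.7 and 10.7% at 0.8.

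**The case against.** The strongest reply is that the label does no inferential work. One primary test is planned, the paired t-test on the mean change. The study is sized on that test, and the secondary analyses list no proportion improved. The two lines can be read as explaining which direction of the difference is favourable, or as feedback for individuals, since Step four returns scores to participants so they can follow their own progress. On that reading the remedy largely restates what the Primary analysis section already does.

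Most of this stands, and it limits the point. A reader might infer that the study has a 35–45% false-positive rate. It does not: that rate belongs to an individual label, and the t-test is separate. A reader might also infer that a share improved will be the headline result, but the article does not commit to reporting one.

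The reply does not rescue the rule. It is written out under the primary outcome, it says what is to be concluded about each participant, and as a statement about individual knowledge it is wrong whether or not the labels are ever counted.

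A second objection is that any percentage depends on quiz features the article does not supply. That is correct. The chance rate is not a fixed property of the rule, and nothing says the quizzes are short. Likewise, quoting 11% at ceiling would pick the top of a 0.6–11% range under assumed 10-item quizzes.

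**Conclusion.** The point holds as a fault in an individual-level rule. As written, the rule turns any rise in score, however small, into improved knowledge. Assuming two equally difficult quizzes of 5–30 items with 50–80% correct, about 34–45% of participants (14 to 18 of 40) would be labelled improved with no learning. Over 3–30 items and 50–95% correct the figure is about 12–45%. Unequal difficulty of 5–10 points takes it from about 20% to 71% in the cases examined (70% correct on the first quiz, 5–20 items). Quiz length, percent correct and relative difficulty are all assumptions.

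The documents do not support reading this as a defect of the primary test or of the sample size, both of which stand apart from the label. Nor do they fully support saying that the best performers are declared non-learners: the wording is that no progress is observed, which is literally true of someone already at full marks. The ceiling is a limit of the score itself and affects the mean change as well.

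**What to change.** Delete the improved / no-progress rule as an indicator of effectiveness, and state that the effectiveness conclusion rests on the mean paired change of the Primary analysis section, reported with its 95% confidence interval.

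If a proportion is still wanted, report the percentages higher, tied and lower together, and compare higher with lower by a sign test. With 10 items at 70% correct and no learning, about 16 of 40 would be higher, 8 tied and 16 lower, which shows at once that nothing has happened. The sign test's null of equal shares needs quizzes of equal length as well as equal difficulty: with 10 then 9 items at 70% correct, 45.9% would be higher and about 54.0% lower by chance.

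The cost is two lines of text and no new data; the article states that recruitment had not begun. The downside is the loss of one easily communicated figure. The change does not remove ceiling effects or bias from unequal quiz difficulty, which affect the mean change and the sign test too. Both should be stated as limits when the mean change is interpreted.
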